## Abstract

**Introduction:**

ACOSOG-Z0011(Z11) trial showed that axillary node clearance (ANC) may be omitted in women with ≤2 positive nodes undergoing breast conserving surgery (BCS) and whole breast radiotherapy (RT). A confirmatory study is needed to clarify the role of axillary treatment in women with ≤2 macrometastases undergoing BCS and groups that were not included in Z11 for example, mastectomy and those with microscopic extranodal invasion. The primary objective of POsitive Sentinel NOde: adjuvant therapy alone versus adjuvant therapy plus Clearance or axillary radiotherapy (POSNOC) is to evaluate whether for women with breast cancer and 1 or 2 macrometastases, adjuvant therapy alone is non-inferior to adjuvant therapy plus axillary treatment, in terms of 5-year axillary recurrence.

**Methods and analysis:**

POSNOC is a pragmatic, multicentre, non-inferiority, international trial with participants randomised in a 1:1 ratio. Women are eligible if they have T1/T2, unifocal or multifocal invasive breast cancer, and 1 or 2 macrometastases at sentinel node biopsy, with or without extranodal extension. In the intervention group women receive adjuvant therapy alone, in the standard care group they receive ANC or axillary RT. In both groups women receive adjuvant therapy, according to local guidelines. This includes systemic therapy and, if indicated, RT to breast or chest wall. The UK Radiotherapy Trials Quality Assurance Group manages the in-built radiotherapy quality assurance programme. Primary endpoint is 5-year axillary recurrence. Secondary outcomes are arm morbidity assessed by Lymphoedema and Breast Cancer Questionnaire and QuickDASH questionnaires; quality of life and anxiety as assessed with FACT B+4 and State/Trait Anxiety Inventory questionnaires, respectively; other oncological outcomes; economic evaluation using EQ-5D-5L. Target sample size is 1900. Primary analysis is per protocol. Recruitment started on 1 August 2014 and as of 9 June 2021, 1866 participants have been randomised.

**Ethics and dissemination:**

Protocol was approved by the National Research Ethics Service Committee East Midlands—Nottingham 2 (REC reference: 13/EM/0459). Results will be submitted for publication in peer-reviewed journals.

**Trial registration number:**

ISRCTN54765244; NCT0240168Cite Now

Strengths and limitations of this studyPOsitive Sentinel NOde: adjuvant therapy alone versus adjuvant therapy plus Clearance or axillary radiotherapy (POSNOC) includes women undergoing mastectomy and those with extranodal invasionOnly women with 1 or 2 macrometastases are eligible for randomisation.POSNOC has an in-built radiotherapy quality assurance programme co-ordinated by the UK Radiotherapy Trials Quality Assurance Group.POSNOC is an international trial—UK, Australia and New Zealand.

## Introduction

Currently, women with early breast cancer and 1 or 2 macrometastases in sentinel lymph nodes (SNs) generally undergo some form of axillary treatment, either surgical axillary node clearance (ANC) or radiotherapy to the axilla (ART). The use of axillary treatment is based on the assumption that it reduces the risk of axillary recurrence and might improve survival. However, axillary treatment damages lymphatic drainage from the arm and women can subsequently develop lymphoedema, restricted shoulder movement, pain, numbness, and other sensory problems. These adverse effects interfere with daily activities, are distressing, impair quality of life (QoL) and are costly to the NHS (National Health Service) in terms of rehabilitative treatments, as they are often permanent and symptom relief is difficult.

Axillary treatment may no longer be necessary for this group of women, as they usually have a low axillary tumour burden and current systemic therapy is effective at preventing breast and axillary recurrence.^1^ Also, sentinel node biopsy has already removed the lymph nodes most likely to have metastasis.^2^ Moreover, when adjuvant therapy includes radiotherapy (RT) to the breast or chest wall, the lower axilla may be treated as it is often included in the tangential irradiation field, and some lower level axillary nodes may be removed at mastectomy.^3^

This hypothesis is supported by the Z11 trial^4^ that showed that ANC may be omitted in women with ≤2 positive nodes undergoing breast conserving surgery (BCS) and receiving whole breast RT. Axillary recurrence was low, and there were no clear differences between the two groups (ANC 0.5% vs no ANC 0.9%) at 6.3 years. Z11 has not had the desired impact on change of clinical practice because of several limitations. The study did not meet its recruitment goal, approximately 40% of participants had micrometastases, many were lost to follow-up (19.4%), and there was a lack of radiation therapy quality assurance. Most US radiation oncologists continue to treat the undissected axilla in women with micro or macro metastases with ART.^5^ Therefore, it appears that clinicians in the US are interpreting Z11 in line with AMAROS (After Mapping of the Axilla: Radiotherapy Or Surgery?) study which showed that ART is a less morbid alterative to axillary lymph node dissection in women with low volume nodal disease^6^ rather than omitting axillary treatment. Furthermore, the results are not applicable to subgroups that were not included such as those with mastectomy and microscopic extranodal invasion.

## Objective

The primary objective of the POsitive Sentinel NOde: adjuvant therapy alone versus adjuvant therapy plus Clearance or axillary radiotherapy (POSNOC) trial is to evaluate whether, for women with early breast cancer and one or two nodes with macrometastases, adjuvant therapy alone is non-inferior to adjuvant therapy plus axillary treatment (ANC or ART), in terms of 5-year axillary recurrence.

## Methods and analysis

### Design

POSNOC is a pragmatic randomised, multicentre, non-inferiority, international (UK, Australia, New Zealand) trial. Target sample size is 1900 participants, with 5-year follow-up. Flow of participants through the trial is summarised in figure 1.

**Figure 1 F1:**
[figure not shown]
Trial flow chart. ANC, axillary node clearance; ART axillary radiotherapy; FACT B+4, Functional Assessment of Cancer Therapy—Breast +4; STAI, State/Trait Anxiety Inventory; LBCQ, Lymphoedema and Breast Cancer Questionnaire; QuickDASH, disabilities of the arm, shoulder and hand questionnaire.

### Randomisation

Participants are allocated via a secure internet-based system, using minimisation that is weighted toward minimising imbalance between trial arms with probability 0.8. Allocation is stratified by recruiting site and minimised by the following variables: age (<50, ≥50 years); type of breast surgery (BCS, mastectomy); oestrogen receptor status (ER) (positive, negative); number of positive nodes (1, 2); intraoperative sentinel assessment using OSNA (One-step nucleic acid amplification) (yes, no).

### Target population

Women with unifocal or multifocal invasive breast cancer with the largest lesion ≤5 cm, who have 1 or 2 sentinel nodes with macrometastases (>2 mm), with or without extranodal invasion.

Women are usually screened for eligibility after their initial breast surgery and sentinel node biopsy. In hospitals where sentinel node histology is assessed intra-operatively, women are asked to give their consent preoperatively and then randomised intra-operatively if their sentinel nodes are found to be positive.

### Inclusion criteria

Women are eligible for inclusion if all of the following criteria apply:

18 years or older.Unifocal or multifocal invasive tumour ≤5 cm in its largest dimension, measured pathologically or largest invasive tumour diameter on radiology for women who are randomised intra-operatively or who undergo sentinel node biopsy before neoadjuvant therapy (tumour size is based only on the single largest tumour).At sentinel node biopsy have 1 or 2 nodes with macrometastases (tumour deposit >2.0 mm in largest dimension or defined as macrometastases on molecular assay).Fit for axillary treatment and adjuvant therapy.Have given informed consent.

### Exclusion criteria

Women are excluded if they have any of the following:

bilateral invasive breast cancer,more than 2 nodes with macrometastases,neoadjuvant therapy for breast cancer exceptif sentinel node biopsy performed prior to neoadjuvant therapy in women with early breast cancer,short duration of neoadjuvant endocrine therapy (up to 3 months),previous axillary surgery on the same body side as the scheduled sentinel node biopsy,not planned to receive adjuvant systemic therapy,previous cancer less than 5 years previously or concomitant malignancy exceptbasal or squamous cell carcinoma of the skin,in situ carcinoma of the cervix,in situ melanoma,contralateral or ipsilateral in situ breast cancer.

### Trial treatment arms

All participants receive adjuvant therapy according to local guidelines. This includes chemotherapy and/or endocrine therapy for all women, and RT to breast or chest wall if indicated. Human epidermal growth factor receptor 2 targeted treatment is administered when indicated.

Trial participants are allocated to one of the following two groups:

Adjuvant therapy alone (intervention group)

See above for adjuvant therapy. Axillary and supraclavicular fossa RT is not allowed.

Adjuvant therapy plus axillary treatment (standard care group)

See above for adjuvant therapy. Axillary treatment can be ANC or axillary RT as per local guidelines.

### Outcomes

#### Primary outcome

The primary outcome is 5-year axillary recurrence defined as pathologically (cytology or biopsy) and/or radiologically confirmed recurrence in lymph nodes draining the primary tumour site, i.e. nodes in the ipsilateral axilla, infraclavicular fossa, supraclavicular fossa and interpectoral area.

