Arm morbidity assessed by (1) Lymphoedema and Breast Cancer Questionnaire^7^—the definition of lymphoedema is ‘yes’ to the two questions—‘heaviness during the past year’ and ‘swelling now’; (2) QuickDASH questionnaire^8^—shoulder, arm and hand disability is defined as a change from baseline in the QuickDASH score of at least 14 points.QoL assessed by Functional Assessment of Cancer Therapy-Breast+4 (FACT B+4) questionnaire.^9^ The total FACT B+4 score reflects global QoL and comprises physical (7 items), functional (7 items), social (7 items) and emotional well-being (6 items) plus the breast cancer concerns and arm morbidity scale (14 items) (total of 41 items; total score ranges from 0 to 164). The 5 item arm morbidity subscale score comprises the sum of the scores from items B3, B10, B11, B12, B13 (range 0–20) and will be analysed separately. Analyses will include the proportion of participants in the two allocated treatment groups reporting ‘somewhat’, ‘quite a bit’ and ‘very much’ for each of the 5 items.Anxiety assessed by using the Spielberger State/Trait Anxiety Inventory (STAI).^10^ The STAI consists of 2 questionnaires with 20 items. It assesses anxiety proneness (Trait) and the current state of anxiety or anxiety change (State). Each item is rated on a four point Likert scale. High STAI scores signify greater anxiety. The Trait anxiety is measured only once and the State at each time point.Economic outcomes will include costs to the NHS, quality-adjusted life years (QALYs) based on responses to the EQ-5D-5L, and the primary outcome, axillary recurrence. For more details, see Economic Analysis section below.Local (breast or chest wall) recurrence; defined as pathologically (cytology or biopsy) and/or radiologically confirmed recurrence after mastectomy in the skin or soft tissue of the chest wall within the anatomical area bounded by the mid-sternal line, the clavicle, the posterior axillary line and the costal margin or any type of breast carcinoma in the breast after conservation therapy.Regional (nodal) recurrence; defined as pathologically (cytology or biopsy) and/or radiologically confirmed recurrent tumour in the lymph nodes in the ipsilateral axilla, infraclavicular, supraclavicular fossa, interpectoral area or ipsilateral internal mammary chain.Distant metastasis; defined as confirmed metastasis (positive pathology and/or definitive evidence on imaging) in all other sites of recurrence and may include those classified as: soft-tissue category, visceral category, central nervous system and skeletal spread.Time to axillary recurrence is the time between the date of randomisation and the date of axillary recurrence, measured in days.Axillary recurrence free survival is the time between the date of randomisation and date of confirmed axillary recurrence or date of death, whichever comes first, measured in days.Disease free survival; defined as the time between the date of randomisation and the date of disease progression (ie, local or regional recurrence or distant metastasis) or death, whichever comes first, measured in days.Overall survival is the time between the date of randomisation and the date of death from any cause.Contralateral breast cancer is new primary malignancy in the opposite breast unless obviously contiguous with recurrent chest wall disease or proven on cytology/biopsy to be of metastatic origin.Non-breast cancer is any new non-breast primary malignancy, except for adequately treated, superficial squamous or basal cell carcinoma of the skin, or carcinoma in situ of the cervix.

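### Primary and regional recurrence are defined by lymph nodes only, so a soft-tissue recurrence in the ipsilateral axilla is not a primary event and is coded as local or distant disease

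*Protocol article*

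**What the plan says.** Four definitions in the protocol article bear on this point.

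- **Primary outcome** (Outcomes, Primary outcome): the event may be shown by pathology or by imaging, and the text reads "radiologically confirmed recurrence in lymph nodes draining the primary tumour site, i.e. nodes in the ipsilateral axilla". Three further nodal sites complete the list: both fossae adjoining the clavicle and the interpectoral area.
- **Regional recurrence** (Secondary outcomes): "recurrent tumour in the lymph nodes in the ipsilateral axilla, infraclavicular, supraclavicular fossa, interpectoral area or ipsilateral internal mammary chain". This adds the internal mammary chain but is still confined to nodes.
- **Local recurrence** (Secondary outcomes): after mastectomy, a bounded site described as "skin or soft tissue of the chest wall within the anatomical area bounded by the mid-sternal line, the clavicle, the posterior axillary line", with a lower limit at the costal margin; after conservation, "any type of breast carcinoma in the breast after conservation therapy".
- **Distant metastasis** (Secondary outcomes): confirmed disease "in all other sites of recurrence and may include those classified as: soft-tissue category", followed by visceral, central nervous system and skeletal categories.

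On treatment, the standard-care arm is described thus: "Axillary treatment can be ANC or axillary RT as per local guidelines" (Trial treatment arms). The intervention arm has neither.

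**The concern.** The trial asks whether the axilla stays controlled without axillary treatment. Its primary event is nevertheless defined by tissue type (node) as well as by site. A confirmed deposit in the soft tissue of the axilla meets neither the primary nor the regional definition, and the remaining categories place it in local or distant disease. A failure of axillary control could therefore be counted as a distant metastasis.

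The classification may also depend on the randomised treatment. Clearance removes most of the nodes in which a recurrence could be called nodal, and by design it is given only in standard care. If non-nodal recurrence makes up a larger share of axillary failures after clearance than in an uncleared axilla, the definition drops more events from standard care. The observed difference would then move against adjuvant therapy alone, and a treatment that is truly non-inferior would be less likely to be shown so. Time to axillary recurrence, axillary recurrence free survival and the cost per reduction in axillary recurrence rest on the same event. Local recurrence or distant metastasis would receive the displaced events.

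**Working it through.** **Step 1: where does a non-nodal axillary deposit go?**

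| Category | After breast conservation | After mastectomy |
|---|---|---|
| Primary event | No: not in a node | No: not in a node |
| Regional | No: not in a node | No: not in a node |
| Local | No: breast only | Only if read as chest wall |
| Distant | Yes: all other sites, soft tissue | Yes, if not read as chest wall |

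**Step 2: reproduce the plan's sample size.** Inputs from the Sample size section: 2% control recurrence, margin 2 percentage points, Miettinen-Nurminen score interval, one-sided alpha 2.5%, power 80%, 850 analysed per arm. The true difference is taken as 0, which is an assumption because the article does not state it.

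Let x and y be the events among 850 in the intervention and standard-care arms, p1 = x/850 and p2 = y/850. Let P1 and P2 be the maximum likelihood estimates restricted to P1 − P2 = 0.02. Then

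Z = (p1 − p2 − 0.02) / √{ [P1(1 − P1) + P2(1 − P2)]/850 × 1700/1699 }

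Non-inferiority is declared when Z ≤ −1.96. Power is the sum of the binomial probabilities of all pairs (x, y) that meet this. At 2% v 2% it is 80.6%. At a true 4% v 2% the chance of declaring non-inferiority is 2.4%. For the randomised target, 1700/(1 − 0.10) = 1889, rounded to 1900. The stated sample size is therefore sound.

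**Step 3: loss of control events only (illustration).** Let f be the share of standard-care axillary recurrences that are soft-tissue only. It is not in the document, so a range is shown. The observed control rate is 2% × (1 − f), and the events lost are 850 × 0.02 × f = 17f.

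| f | Observed rates | Control events lost | Shift in difference | Power | False non-inferiority at true 4% v 2% |
|---|---|---|---|---|---|
| 0 | 2.0% v 2.0% | 0 | 0 | 80.6% | 2.4% |
| 5% | 2.0% v 1.9% | 0.85 | +0.1 points | 77.2% | 1.8% |
| 10% | 2.0% v 1.8% | 1.7 | +0.2 points | 73.5% | 1.3% |
| 20% | 2.0% v 1.6% | 3.4 | +0.4 points | 65.0% | 0.7% |
| 30% | 2.0% v 1.4% | 5.1 | +0.6 points | 55.2% | 0.3% |

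The last column assumes that the intervention arm loses nothing, so that 4% is still observed there.

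**Step 4: lower event rate.** The Introduction cites an earlier trial with 0.5% and 0.9% axillary recurrence at 6.3 years. At 1% v 1% power is 96.2%. With 30% of control events lost (1% v 0.7%) it is 91.5%.

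**Step 5: equal loss in both arms.** At 1.8% v 1.8% (10% lost from each) power is 84.0%, so it does not fall. A true 4% v 2% would then be recorded as 3.6% v 1.8%, and false non-inferiority would be 4.1% instead of 2.4%.

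**Step 6: how few events decide the result.** With 850 per arm, 17 control events (850 × 2%) allow up to 21 intervention events for non-inferiority, and 15 control events allow up to 19.

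These figures use the unadjusted score test. The planned mixed model was not simulated.

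**The case against.** Several arguments limit the point.

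- **Direction.** A reader might infer that the events are lost from standard care only. The article does not show that. The definition is worded identically for both arms, every participant has had a sentinel node biopsy, and women with extranodal invasion are eligible, so non-nodal axillary disease can arise in the intervention arm too. More frequent loss after clearance is a plausible inference from the design, not a documented fact.
- **Size.** Standard care may be axillary radiotherapy, after which nodes remain, and the other three nodal sites count in both arms. Suppose half of the standard-care events followed clearance (an assumption). A 30% loss overall would then need 60% of post-clearance recurrences to be non-nodal, while 10% of them would mean a 5% loss overall and 77% power. The fall to 55% is the far end of an assumed range, not an estimate.
- **The chest-wall boundary.** It is tempting to say that the local definition takes in the axilla because it runs to the posterior axillary line. The text limits it to "recurrence after mastectomy in the skin or soft tissue of the chest wall within the anatomical area bounded by the mid-sternal line" and the other landmarks. These lines bound chest-wall tissue and do not make the axilla chest wall. The coding after mastectomy is therefore unclear rather than clearly local.
- **Consequence.** A loss weighted to standard care makes false non-inferiority less likely, and the events still count in disease-free survival.
- **Stage of the trial.** By 9 June 2021, 1866 women had been randomised, and the 2% rate and the margin were set for the existing endpoint. Coding guidance may also sit in documents that are not shown.

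All of this stands as a limit on direction and size. It does not remove the definitional gap: the article states all four categories, and as stated they place a soft-tissue axillary recurrence outside both axillary and regional disease.

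**Conclusion.** The point holds as a fault in the definitions. A non-nodal recurrence in the ipsilateral axilla is excluded from the primary and regional events. It is distant after breast conservation, and local or distant after mastectomy. If this happens more often after clearance, the bias is against non-inferiority.

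The size cannot be determined from the document, which gives neither the non-nodal share in either arm nor the split between clearance and radiotherapy. The power losses in the working rest on an assumed control-only loss and are illustrations. The sample size itself is not in error. The matter still deserves action because about 17 control events are expected and a shift of two events can change the conclusion.

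**What to change.** Before unblinding, state that any confirmed recurrence in the ipsilateral axilla, infraclavicular fossa, supraclavicular fossa or interpectoral area, whether in node or soft tissue, is coded as axillary and regional, and not as local or distant. Classify events already recorded by site of disease, blind to allocation.

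If the sponsor prefers to keep the nodal-only primary endpoint at this stage, prespecify a sensitivity analysis that repeats the non-inferiority comparison with the site-based definition.

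The cost is a change of wording in the definitions and coding guidance and a recheck of the few local and soft-tissue events. No new visits, procedures or participants are needed. The drawback of changing the primary definition is a slight departure from the endpoint for which the 2% rate and the margin were set; the sensitivity analysis avoids it.

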#### Secondary outcomes

Secondary outcomes and timepoints of assessment are summarised in table 1.

**Table 1 T1:** Secondary outcomes are assessed at the following time points

Secondary outcome	Assessment time point (months)						
	3	6	12	24	36	48	60
Arm morbidity		X	X	X	X		
Quality of life	X	X	X	X	X		
Anxiety	X	X	X	X	X		
NHS costs	X	X	X	X	X	X	X
EQ-5D-5L	X	X	X	X	X		
Incremental cost per QALY gained					X		
Incremental cost per reduction in axillary recurrence							X
Local (breast or chest wall) recurrence		X	X	X	X	X	X
Regional (nodal) recurrence		X	X	X	X	X	X
Distant metastasis		X	X	X	X	X	X
Time to axillary recurrence		X	X	X	X	X	X
Axillary recurrence free survival		X	X	X	X	X	X
Disease free survival		X	X	X	X	X	X
Overall survival		X	X	X	X	X	X
Contralateral breast cancer		X	X	X	X	X	X
Non-breast malignancy		X	X	X	X	X	X

QALY, quality-adjusted life year.

Arm morbidity assessed by (1) Lymphoedema and Breast Cancer Questionnaire^7^—the definition of lymphoedema is ‘yes’ to the two questions—‘heaviness during the past year’ and ‘swelling now’; (2) QuickDASH questionnaire^8^—shoulder, arm and hand disability is defined as a change from baseline in the QuickDASH score of at least 14 points.QoL assessed by Functional Assessment of Cancer Therapy-Breast+4 (FACT B+4) questionnaire.^9^ The total FACT B+4 score reflects global QoL and comprises physical (7 items), functional (7 items), social (7 items) and emotional well-being (6 items) plus the breast cancer concerns and arm morbidity scale (14 items) (total of 41 items; total score ranges from 0 to 164). The 5 item arm morbidity subscale score comprises the sum of the scores from items B3, B10, B11, B12, B13 (range 0–20) and will be analysed separately. Analyses will include the proportion of participants in the two allocated treatment groups reporting ‘somewhat’, ‘quite a bit’ and ‘very much’ for each of the 5 items.Anxiety assessed by using the Spielberger State/Trait Anxiety Inventory (STAI).^10^ The STAI consists of 2 questionnaires with 20 items. It assesses anxiety proneness (Trait) and the current state of anxiety or anxiety change (State). Each item is rated on a four point Likert scale. High STAI scores signify greater anxiety. The Trait anxiety is measured only once and the State at each time point.Economic outcomes will include costs to the NHS, quality-adjusted life years (QALYs) based on responses to the EQ-5D-5L, and the primary outcome, axillary recurrence. For more details, see Economic Analysis section below.Local (breast or chest wall) recurrence; defined as pathologically (cytology or biopsy) and/or radiologically confirmed recurrence after mastectomy in the skin or soft tissue of the chest wall within the anatomical area bounded by the mid-sternal line, the clavicle, the posterior axillary line and the costal margin or any type of breast carcinoma in the breast after conservation therapy.Regional (nodal) recurrence; defined as pathologically (cytology or biopsy) and/or radiologically confirmed recurrent tumour in the lymph nodes in the ipsilateral axilla, infraclavicular, supraclavicular fossa, interpectoral area or ipsilateral internal mammary chain.Distant metastasis; defined as confirmed metastasis (positive pathology and/or definitive evidence on imaging) in all other sites of recurrence and may include those classified as: soft-tissue category, visceral category, central nervous system and skeletal spread.Time to axillary recurrence is the time between the date of randomisation and the date of axillary recurrence, measured in days.Axillary recurrence free survival is the time between the date of randomisation and date of confirmed axillary recurrence or date of death, whichever comes first, measured in days.Disease free survival; defined as the time between the date of randomisation and the date of disease progression (ie, local or regional recurrence or distant metastasis) or death, whichever comes first, measured in days.Overall survival is the time between the date of randomisation and the date of death from any cause.Contralateral breast cancer is new primary malignancy in the opposite breast unless obviously contiguous with recurrent chest wall disease or proven on cytology/biopsy to be of metastatic origin.Non-breast cancer is any new non-breast primary malignancy, except for adequately treated, superficial squamous or basal cell carcinoma of the skin, or carcinoma in situ of the cervix.
